## Abstract

**Background:**

There is growing evidence that Internet-based cognitive behavioral therapy (ICBT) is as effective as a stand-alone treatment and helps facilitating access to treatment. Given the complexity of the treatment, we argue that the effect of ICBT could be even greater if guided by a therapist, as this could increase treatment adherence. We modified an established and well-evaluated treatment approach and developed a mobile application for treating social anxiety disorder (SAD). In the present study, we compare the efficacy of app use alone (APP) with video-based, therapist-guided app use (TG-APP) and with a wait-list control group (WLC) in terms of symptom reduction, and various secondary outcomes such as increase in quality of life or decrease of general psychological distress.

**Methods/design:**

A within-between interaction design with randomization to one of three conditions will be used. In the APP condition, patients receive only the app without any additional contact with therapists, while in the TG-APP condition, therapists provide 8 sessions of video-based treatment in addition to using the app. The study will be conducted in two university outpatient treatment centers with reliably diagnosed SAD patients. The primary outcome will be defined as change in SAD symptoms, as measured by the Liebowitz Social Anxiety Scale (expert rating). Furthermore, a wide range of self-reports and clinician ratings for other symptoms (depression, general psychopathology) or quality of life will be used. A simulation-based power analysis for a 3 × 2 interaction effect (group × time) on the primary outcome in a linear mixed model resulted in a total sample size of *N* = 165.

**Discussion:**

The present study will be one of the first to examine the additional benefit of therapist-guided video sessions regarding the use of an app treating SAD. Study results are pivotal to future treatment application in SAD.

**Supplementary Information:**

The online version contains supplementary material available at 10.1186/s13063-023-07168-5.

## Introduction

Social anxiety disorder (SAD) is characterized by the fear of behaving in a way that is negatively perceived by others [1]. In the USA, the disorder has a lifetime prevalence of 10.7% and a 12-month prevalence of 7.4% [2]; in Europe, the estimated lifetime prevalence is 6.7% [3]. The disorder is associated with high psychosocial impairment and disability [3].

On the one hand, there are ways to treat SAD. For example, a recent meta-analysis demonstrated that individualized cognitive therapy (CT) based on the model of Clark and Wells [4] was among the most effective treatments, outperforming pharmacotherapy and other psychotherapeutic approaches in several studies [5]. On the other hand, although treatment is recommended in international guidelines, access to effective treatment for SAD patients remains difficult, in part because SAD-related anxiety and impairment exacerbate difficulties and delays in initial treatment contact [6–8].

Addressing these treatment barriers, Lee and Stapinski [9] found evidence that social anxiety is related to a perception of decreased risk of negative evaluation and greater control in online communication. Therefore, Internet-delivered cognitive-behavioral treatments (ICBTs) may be a promising approach to the treatment of SAD. ICBTs may reduce the threshold to seek treatment and provide cost-efficient [10, 11] and highly scalable access to scientifically evaluated treatment programs [12]. Recent empirical data shows that internet-based cognitive behavioral treatments can be as effective as traditional face-to-face therapy [12, 13] and also reach favorable long-term outcomes [12, 14]. Stott et al. [15] for example were able to show that an online treatment program, based on the Clark and Wells approach, offered through a website, was significantly reducing SAD-related symptoms.

Previous studies that have examined the effectiveness of ICBTs have largely used treatment programs delivered via a computer. Today, however, the use of a smartphone including its apps is even more widespread, rendering mobiles a promising option for the treatment of mental disorders. It might even have more advantages than ICBTs delivered via a computer, as apps seem to be easily integrated into daily routines [16] and are convenient for both the patient and the practitioner [17]. Furthermore, using a mobile phone has the advantage that patients can use protocols or other forms of assessments when the situation occurs so that some forms of perception and reporting biases can be minimized [18]. As an example, Stolz et al. [16] have been able to show that an app based on the Clark and Wells [4] treatment approach with text-based guidance during the process can significantly reduce symptoms of social anxiety. However, it remains unclear whether their app would also work without additional guidance.

This raises the important research question of whether the effectiveness of apps can be enhanced by accompanying face-to-face sessions with a therapist. To date, few studies have addressed this question. The authors assume that therapist guidance could additionally increase compliance with ICBT treatment as well as the motivation to complete it. Another advantage of therapist-guided ICBT over nonguided ICBT could be higher patient safety, as the therapist can assist when questions or ambiguities arise, or when adverse side effects of ICBT occur, such as worsening of symptoms, negative well-being, or noncompliance [19].

Particularly as a result of the COVID-19 pandemic, new ways of providing therapeutic support have been developed: Due to the limitations of physical contact, the use of videoconferencing has increased dramatically. A meta-analysis has shown that video-based psychotherapy typically has large effect sizes and that the difference to in-person therapy is negligible [20]. The use of this modality to treat mental disorders could be an important step in increasing accessibility to psychotherapy, not only because of the ongoing (or possibly recurring) pandemic situation, but also to overcome other barriers to in-person treatment, such as illnesses that limit the scope of activities, specialized treatment programs that exist only in distant locations, or difficulty finding a therapist in rural areas.

In summary, the use of ICBT delivered via a smartphone application could improve the accessibility of psychotherapy and integrate interventions into everyday life, making it a promising approach for the future treatment of SAD. However, few studies have attempted to implement Clark and Wells’ [4] well-evaluated approach into a treatment program in form of an app, and even fewer have examined whether the app works without further guidance. Therefore, our goal was to develop and evaluate an app that could effectively help patients without therapeutic support. In addition, questions remain about how the app and face-to-face therapy can be combined and how this combined treatment compares to using the app alone. We aim to investigate these questions in a randomized controlled trial focusing on (1) the overall efficacy of a newly developed app for SAD and (2) the potential benefit of additional therapeutic support delivered via videoconferencing.

### Objectives

The main goal of the present study is to evaluate whether the use of the app-based intervention helps to decrease symptoms of social anxiety disorder and has positive effects on mental health. There will be two experimental treatment conditions: App-based CT (APP) and app-based CT plus 8 therapist-guided video-delivered therapy sessions (TG-APP). Both will be compared to a wait-list control group (WLC). The therapists will be trained in Cognitive Therapy based on the model of Clark and Wells [4], which has been proven to be effective in face-to-face therapy [5] and in ICBT [15]. In a randomized controlled trial (RCT), the following hypotheses will be tested:Hypothesis 1a: In the APP and TG-APP condition, SAD-related symptoms, as measured by the LSAS, will decrease significantly more from baseline to post-treatment than in the WLC condition.Hypothesis 1b: The TG-APP condition results in a significantly greater reduction in SAD-related symptoms, as measured by the LSAS, than the APP and the WLC conditions, from baseline to post-treatment.Hypothesis 1c: In the APP and the TG-APP condition, there will be no significant deterioration of SAD-related symptoms, as measured by the LSAS, from post-treatment to follow-up.Hypothesis 2a: In the APP and TG-APP conditions, significant improvements in secondary outcome variables, including social phobic cognitions, depression symptoms, general psychological distress, psychological impairment, quality of life, and interpersonal pleasure, are achieved from baseline to post-treatment compared to the WLC condition.Hypothesis 2b: In the TG-APP condition, improvements in secondary outcome variables from baseline to post-treatment will be significantly larger than in the APP condition.Hypothesis 2c: In the APP and TG-APP condition, there will be no significant deterioration in secondary outcome variables from post-treatment to follow-up.Hypothesis 3: Individual learning styles contribute significantly to predicting success in both treatment conditions.Hypothesis 4: The increase in social approach behavior will mediate the effect of the TG-APP versus APP condition.

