### Trial design

The design of the planned bi-centric randomized controlled superiority trial will be based on a within-between interaction group design with three groups (WLC, APP, TG-APP) and parallel group assignment. The primary outcome criterion is the change in symptom severity of SAD, as measured by the Liebowitz Social Anxiety Scale (LSAS) [21, 22]. It will be assessed by trained, blinded, independent raters at pre-treatment, post-treatment, and 6 months after post-treatment (follow-up). The planned allocation ratio for TG-APP vs. APP only vs. WLC will be 1:1:0.7.

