We based our power analysis on an iterative simulation of increasing sample sizes with starting values of *n* = 30 for the control condition and *n* = 50 for each of the treatment conditions, increasing stepwise by one participant per condition. The variance of the random intercepts and residual variance was set to 0.5 respectively [24]. Because missing values due to the dropout of participants were planned to be imputed by the jump to reference method (J2R) [25], the reference being the control condition, we reduced our expected effected sizes by multiplying them with the term (1—dropout-rate). Given a dropout rate of 26% at post-treatment evaluation in the study by Stolz et al. [16] and a pooled post-treatment dropout rate of 26.2% in a meta-analysis of studies using smartphone apps by Torous et al. [26], we chose a conservative estimate of 30% post-treatment dropout for the APP condition and multiplied the expected effect size of 0.5 by 0.7, equaling to *d* = 0.35. For the TG-APP condition, we expected a lower post-treatment dropout rate of 20% due to the additional guidance by a therapist and multiplied the expected effect size of 0.8 by 0.8, equaling to *d* = 0.64. Based on 500 simulations of the linear mixed model fitted with the expected effect sizes, we obtained the power of finding a statistically significant interaction of group × time based on a likelihood ratio test, compared to finding only main effects, and the 95% confidence interval for this estimate, for increasing sample sizes. We located the minimum sample size in our results after which the lower bound of the 95% confidence interval did not fall below 80% power, given *α* = 0.05. This condition was met at *n* = 41 for the control group and *n* = 61 for both treatment conditions (power estimate = 84%, 95% confidence interval = 80.0, 87.0). In addition to our study purposes, the app provider intends to use the results of the pilot study and the main study for the licensing process of the app as a digital health product. For this licensing process, a separate statistical analysis will be conducted comparing only the APP condition with the WLC condition, using a *t*-test for statistical analysis. A corresponding additional sample size calculation revealed the need to recruit 43 subjects in the wait-list control group (WLC). To establish conformity across the planned analyses we adjusted the number of participants for WLC upward to *n* = 43, resulting in a total sample size of *N* =165 (see also Fig. 1).

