#### Secondary analyses

As secondary analyses, we will evaluate treatment effects (from baseline to post-treatment, as described in hypothesis 2a and from post-treatment to follow-up, as described in hypothesis 2c) on quality of life, as measured by the WHO-QOL-BREF, interpersonal pleasure, as measured by the ACIPS, further SAD-related symptoms, as measured by the SPIN and the CGI, social phobic cognitions, as measured by the SPK, symptoms of depression, as measured by the BDI-FS and the QIDS-C, general psychological distress, as measured by the BSI, and limitations in everyday life, as measured by the PDI. We will also assess adverse effects measured by the self-developed adverse effect scale. Moreover, we will compare posttreatment LSAS scores with scores at follow-up, as stated in hypothesis 1c, using the linear mixed model described earlier.

To control for moderating effects on decreases in social anxiety symptoms, as indicated in hypothesis 3, we include the scores of the individual learning style, as measured by Kolb’s LSI and experienced pain in social situations, as measured by the SPQ-5, as predictors in the model and specify three-way interactions with treatment conditions and time for all these factors. We will conduct a similar analysis to test whether social approach behavior measured by the SPWSS has a mediating effect on social anxiety symptoms, as we hypothesized in hypothesis 4. We will test all interactions by comparing the full to a reduced model without the respective interaction term via likelihood ratio tests (LRTs) [62] and remove all non-significant interactions from the final model.

To evaluate effects between two conditions at a given time, e.g., between the APP and TG-APP conditions at post-treatment, as indicated in hypothesis 1b and 2b, we will calculate the statistical significance of pairwise differences in LSAS based on the linear mixed model using the R package “emmeans” [63].

We will fit all measures as outcome variables in linear mixed models including the same predictors as in the primary analysis and add the average weekly time participants spent using the app and the number of behavioral experiments conducted as additional explanatory predictors.

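### Hypotheses 1c and 2c count a non-significant change from post-treatment to follow-up as support, with no margin, so absence of evidence would stand in for evidence of no deterioration

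*Protocol article*

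**What the plan says.** The Objectives section lists Hypotheses 1c and 2c among those to be tested. For APP and TG-APP, 1c states that "there will be no significant deterioration of SAD-related symptoms, as measured by the LSAS, from post-treatment to follow-up". Hypothesis 2c has the same form: "there will be no significant deterioration in secondary outcome variables from post-treatment to follow-up".

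The Secondary analyses section gives the test for 1c: "we will compare posttreatment LSAS scores with scores at follow-up, as stated in hypothesis 1c, using the linear mixed model described earlier". Effects on the secondary outcomes are also evaluated "from post-treatment to follow-up, as described in hypothesis 2c". The article gives no margin for acceptable worsening, no equivalence or non-inferiority test and no rule based on a confidence limit. The Trial design section describes a "planned bi-centric randomized controlled superiority trial".

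The sample size rests on the group × time interaction from baseline to post-treatment. The robustness check that adds follow-up is also a group × time interaction (3 × 3). Neither gives power for a within-arm change from post-treatment to follow-up.

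**The concern.** A hypothesis of no significant deterioration is met whenever the test fails to reject. That happens if scores are stable, and also if they worsen but the contrast is too imprecise to show it. Without a margin the two cases cannot be told apart, and less information makes the favourable result more likely. Hypothesis 2c repeats the criterion for each secondary outcome.

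At stake is what may be said about the state of participants six months after treatment. A report that follows the hypotheses as written could present stability that the data do not establish. This is not detail left to an analysis plan: the fault is in the stated criterion, and repairing it means changing the hypothesis.

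**Working it through.** **Inputs from Design and sample size.** Random-intercept and residual variances 0.5 each; 61 participants per active arm; post-treatment dropout 30% (APP) and 20% (TG-APP); assumed effects 0.5 and 0.8, reduced to 0.35 and 0.64; α = 0.05.

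**Assumptions, because the article does not state them.**
- The SD of a within-person change is √(2 × 0.5) = 1.0. This is derived from the planning variances for baseline to post-treatment and carried over to the later interval.
- The test is two-sided.
- Follow-up dropout is not given, so post-treatment completers are taken as still observed: 61 × 0.7 ≈ 43 (APP) and 61 × 0.8 ≈ 49 (TG-APP).

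**The plan's own figure.** With two time points and a random intercept, the interaction test compares change scores of variance 1.0 across three groups. With n = 41/61/61 and means 0/0.35/0.64:
- weighted mean = (61 × 0.35 + 61 × 0.64)/163 = 0.370
- non-centrality = 41 × 0.370² + 61 × (0.35 − 0.370)² + 61 × (0.64 − 0.370)² = 10.08 (unrounded mean)
- power (χ², 2 df) = 0.819

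The article reports 84% (80.0 to 87.0) from 500 simulations. The recomputed value lies inside that interval, so the reading of the variance inputs is consistent with the plan.

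**Chance of a non-significant result when worsening is real.** With true worsening δ and SE = 1/√n, P = Φ(1.96 − δ√n) − Φ(−1.96 − δ√n). The exact column uses the one-sample t-test.

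| Arm, n | True worsening (SD) | Normal | Exact t |
|---|---|---|---|
| APP, 43 | 0.25 (half of 0.5) | 0.626 | 0.640 |
| TG-APP, 49 | 0.25 | 0.583 | 0.597 |
| APP, 43 | 0.35 (whole reduced effect) | 0.369 | 0.389 |
| TG-APP, 49 | 0.40 (half of 0.8) | 0.200 | 0.217 |

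Both arms non-significant at 0.25 SD each, treating the arms as independent: 0.626 × 0.583 = 0.365 (normal); 0.640 × 0.597 = 0.382 (exact).

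**Sensitivity for APP at 0.25 SD (n = 43, exact).** Change SD 0.7: 37%. Change SD 1.15: 72%. One-sided 5% test at SD 1.0: 51% (47% for TG-APP at n = 49).

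**Role of information.** At 0.25 SD and change SD 1.0, the chance of a non-significant result is 22% with n = 122, 52% with 61, 64% with 43 and 89% with 10.

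**What a margin would require.** Take a true change of zero, change SD 1.0 and an upper limit from a two-sided 95% interval. The margin with 80% power is (1.96 + 0.84)/√n:
- n = 43: 2.80/6.56 = 0.43 SD
- n = 49: 2.80/7 = 0.40 SD

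For a margin of 0.25 SD, power is Φ(0.25√n − 1.96) = 37% (n = 43) and 42% (n = 49), and 80% power needs (2.80/0.25)² ≈ 126 evaluable participants per arm.

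**The case against.** Three stronger readings are tempting, and the document does not support them.

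1. *A reader might infer that stability would be declared in most trials despite losing much of the gain.* That holds arm by arm at 0.25 SD under the assumed SD and a two-sided test. It fails for both arms together (36–38%). It also fails for TG-APP losing half its assumed effect, which is missed in only about 20%. For APP it fails if the change SD is 0.7. The planned effects are contrasts with the control group, so a share of the gain is only a yardstick.

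2. *A reader might infer that dropout always makes the hypothesis easier to meet.* The analysis set is everyone randomised, and jump-to-reference imputation with the control group as reference was planned. Loss before post-treatment dilutes deterioration: 0.25 × 0.7 = 0.175 at n = 61 is non-significant in about 73%. Loss afterwards moves a participant towards the control mean, which can look like deterioration. Wait-list participants may use the app after three months, so the reference at follow-up is itself unclear. The net direction is mixed; only the loss of information consistently favours non-significance.

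3. *A reader might infer that the trial announces a finding of durable benefit.* It does not. The Introduction's aims and the Discussion's expected conclusions concern the app's efficacy and the added value of therapist sessions. The follow-up comparison sits under secondary analyses.

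An unseen analysis plan might also contain a margin. That would help only by replacing the criterion printed here. The objections limit the size and reach of the point. They do not remove the fault: as worded, the hypotheses treat failure to reject as support.

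**Conclusion.** The point holds as a fault of inference in Hypotheses 1c and 2c: a non-significant contrast, with no margin, is the supporting outcome. With change SD 1.0, a two-sided 5% test and 43 and 49 observed at follow-up, a real worsening of 0.25 SD goes undetected in about 63–64% (APP) and 58–60% (TG-APP) of trials, and in both arms together in about 36–38%. Change SD, sidedness and follow-up numbers are assumptions, so these figures illustrate the problem and do not predict the trial's results. The fault itself depends on none of them. It concerns hypotheses outside the primary analysis, and the baseline-to-post test is unaffected.

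**What to change.** Reword Hypotheses 1c and 2c as estimation aims: in each active arm, the change from post-treatment to follow-up is estimated and reported with its 95% confidence interval. State that non-significance will not be read as no deterioration or maintained benefit. Amend the matching sentences under Secondary analyses.

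If such a claim is wanted, allow it only when the upper 95% confidence limit of the worsening lies below a prespecified margin with a stated justification. At the expected observed numbers, only margins of about 0.40 SD (TG-APP) to 0.43 SD (APP) or wider reach 80% power. Unless a margin that wide can be justified, reporting the interval alone is the realistic choice.

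The cost is wording. No extra patients are needed and the primary analysis does not change, but a claim of maintenance becomes harder to make.

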### Allocation and randomization

Randomization is performed using a randomization list in which, based on 165 randomly generated numbers sorted by size, each of the available options is assigned according to the planned sample size (WLC = 43, APP = 61, TG-APP = 61). The list is then sorted by sequential number. A study coordinator who is not involved in the diagnosis or treatment process will enter the subjects into the randomization list according to the order of inclusion. The result is communicated to the patients via email and remains hidden from the clinical evaluators. The email to the participant contains the result and, if the person belongs to one of the two intervention groups, all the necessary information to use the app.

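### The three-arm interaction test assigned to Hypothesis 3 cannot show that learning style matters in both treatment conditions, and the protocol describes H3 as prediction in one place and moderation in others

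*Protocol article*

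**What the plan says.** Three places in the protocol article bear on H3.

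- **Objectives.** H3 reads "Individual learning styles contribute significantly to predicting success in both treatment conditions". This is a statement about prediction, and it names both APP and TG-APP.
- **Self-rating scales.** Kolb's Learning Style Inventory (LSI) is said to be collected to see whether learning style affects how well treatment works. That is effect modification.
- **Secondary analyses.** The analysis is introduced with "To control for moderating effects on decreases in social anxiety symptoms, as indicated in hypothesis 3". LSI and SPQ-5 scores enter "as predictors in the model and specify three-way interactions with treatment conditions and time for all these factors". The test rule is "We will test all interactions by comparing the full to a reduced model without the respective interaction term via likelihood ratio tests", and the plan will then "remove all non-significant interactions from the final model".

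The condition factor has three levels, including the wait list, with planned numbers "WLC = 43, APP = 61, TG-APP = 61". The emmeans comparisons in the same section are assigned to H1b and H2b. They compare mean LSAS between conditions, not learning-style slopes.

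**The concern.** Write b_WLC, b_APP and b_TG for the slope of LSAS change (baseline to post-treatment) on a learning-style score in each arm. Read as prediction, H3 says that b_APP and b_TG are both non-zero. Read as moderation of the treatment effect, and keeping its reference to both conditions, it says that b_APP − b_WLC and b_TG − b_WLC are both non-zero. The null of the planned test is b_WLC = b_APP = b_TG. Rejecting it shows that at least one slope differs from another, without saying which. Failing to reject it does not show that any slope is zero.

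The test result therefore does not map onto the hypothesis, and the pruning rule then removes the term that carries the per-arm information. At stake is an uninterpretable answer to a pre-stated secondary hypothesis.

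**Working it through.** The protocol gives no power or effect size for H3, so there is no stated figure to reproduce. The check asks how often the planned test rejects under patterns that agree or disagree with H3.

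**Inputs from the protocol.** Arm sizes 43/61/61 (Allocation and randomization; sum 165). Alpha 0.05, random-intercept variance 0.5 and residual variance 0.5 (Design and sample size). With two time points the random intercept cancels in the change score, so the variance of change is 2 × 0.5 = 1 and its SD is 1.

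**Assumptions.** One standardised LSI score; slope 0.3 or 0.5 SD of change per SD of score; complete data. The slopes are not in the protocol and are shown as a range.

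**Analytic check.** For arm slopes b_i, the 2-df test has noncentrality Σ n_i (b_i − b̄)², where b̄ is the n-weighted mean slope.

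- Equal slopes in all arms: noncentrality 0 whatever the slope, so rejection is at alpha.
- Slope 0.5 in TG-APP only: b̄ = 61 × 0.5 / 165 = 0.185; noncentrality = 61 × 0.25 − 165 × 0.185² ≈ 9.6; power about 80%.
- Slope 0.5 in WLC only: b̄ = 43 × 0.5 / 165 = 0.130; noncentrality = 43 × 0.25 − 165 × 0.130² ≈ 7.9; power about 71%.
- At slope 0.3 these noncentralities scale by (0.3/0.5)² = 0.36, to about 3.5 and 2.9; power about 36% and 31%.

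**Simulation** (20,000 trials per pattern). Change was regressed on arm, score and arm × score. Each cell gives the rate at slope 0.3 / 0.5.

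| Where the slope exists | Planned three-way test rejects | LSI × time term, pooled over arms, rejects | Slopes in APP and TG-APP both significant |
|---|---|---|---|
| All three arms, equal | 5.5% / 5.7% | 97% / 100% | 41% / 93% |
| APP and TG-APP, equal; none in WLC | 31% / 69% | 80% / 99% | 41% / 92% |
| TG-APP only | 36% / 78% | 30% / 63% | 3% / 5% |
| APP only | 37% / 79% | 30% / 63% | 3% / 5% |
| WLC only | 30% / 71% | 17% / 37% | 0.2% / 0.2% |

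**Reading the table.** Compare the second row with the third and fourth. The planned test rejects somewhat more often when only one treated arm has a slope (36% to 37% at 0.3, 78% to 79% at 0.5) than when both do (31% and 69%). A significant result therefore cannot tell one treated arm from two. These rows do not depend on the reading of H3: with no slope in WLC, a slope in one treated arm fails both the prediction claim and the moderation claim for both conditions.

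The first and last rows do depend on the reading. Equal slopes everywhere satisfy H3 as prediction but not as moderation. A slope in WLC only satisfies it as moderation but not as prediction.

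**The case against.** The strongest reply is that H3 was always meant as moderation. The stated reason for collecting the LSI and the lead-in to the analysis both point that way, and the three-way term belongs to the right family for that question. On that reading, rejecting at about 5% under equal slopes is correct, and testing within-arm slopes would be the error. This stands as a reading. It does not rescue the test, because a 2-df omnibus result still does not show moderation in each treated condition, and the Objectives do not state moderation.

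A second reply is that losing the three-way term does not lose learning style. The plan prunes interactions one by one, and the lower-order LSI × time term would nearly always survive under equal slopes (97% / 100%). This is also correct, so a reader should not infer that a genuine predictor would simply vanish from the model. But that term is not linked to H3 and it pools the wait list. It also rejects in about 30% / 63% of trials when only one treated arm has a slope, so it cannot show an effect in both arms either.

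A reader might also infer that a one-arm effect would be reported as support for H3. The protocol does not say that a significant omnibus test alone settles H3, and a retained three-way model would still yield arm-specific coefficients.

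Lastly, decision rules for secondary hypotheses often sit in an analysis plan that is not shown here. That would answer a complaint about missing detail. Here the article itself fixes the term, the test and the pruning rule for H3.

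**Conclusion.** The stated test does not match the stated hypothesis, and the article describes that hypothesis in two ways. Under either reading the planned test cannot establish an effect in both treated arms. It rejects at about alpha under equal slopes in all arms, and in roughly 36% to 79% of trials when one treated arm alone has a slope.

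The percentages rest on the assumed slopes, one score and complete data. The protocol expects 30% dropout in APP and 20% in TG-APP, and the LSI ranks four items per sentence, so more than one score may be used. Neither changes which null is being tested.

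The stronger conclusion, that the trial will return a wrong verdict on H3, is not supported. It requires fixing H3 as prediction against two other sections, and a decision rule that the article does not state. H3 is secondary; the primary analysis and sample size are untouched. The change is worth making but is not critical.

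**What to change.** Reconcile the Objectives, the Self-rating scales section and the Secondary analyses on what H3 means, then follow one branch.

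- **H3 as prediction.** Test the LSI × time slope (baseline to post-treatment) in APP and in TG-APP from the unpruned three-way model, and require both. Report the three-way test separately, as the question of differential prediction.
- **H3 as moderation.** Reword H3 in the Objectives to say so, and follow the three-way test with the APP-versus-WLC and TG-APP-versus-WLC slope contrasts.

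In either case, do not let removal of non-significant interactions decide H3, and state which LSI score or scores are tested.

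The cost is wording only, with the same data, model and software. The downside is stringency. Requiring both within-arm slopes gives about 41% power at slope 0.3 (93% at 0.5, equal slopes in all arms). On the moderation branch each contrast has standard error √(1/43 + 1/61) = 0.199. A slope difference of 0.3 is then 0.3/0.199 = 1.51 standard errors (power about 33%), and 0.5 is 2.51 (about 71%). The write-up should say that a non-significant result on H3 is weak evidence of no effect.
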